### Sample size calculation

The sample size is determined a priori based on calculations assuming a modest improvement of 30% in symptoms in the YAG group compared to 10% in the sham group [7, 15]. This results in a sample of 66 patients with a standard deviation of 25%, an alpha level of 0.05, and a statistical power of 0.9. To account for a 5% rate of lost follow-up, it was decided to include 70 subjects in the study.

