Although numerous studies have demonstrated the efficacy and safety of YAG laser vitreolysis, there remains controversy among some researchers regarding its widespread clinical use [9]. They argue that, as with any new treatment modality, moderate skepticism is warranted until further research demonstrates a favorable risk/benefit ratio. Additionally, Shah’s research found that objective improvement in patients’ vitreous floaters was 94%, while subjective improvement was only 53%, indicating a clear disconnect between objective and subjective responses that must be taken into account. On the efficacy front, the majority of current research does not rule out the placebo effect, as symptoms of vitreous opacities themselves may improve with gravity and neural adaptation. Complications of YAG laser are also worth paying attention to, such as lens damage, retinal hemorrhage, retinal vein occlusion, and postoperative high intraocular pressure [10–13]. To reduce intraoperative complications, YAG laser vitreolysis is recommended for patients with stable Weiss rings, with floaters located more than 2 mm away from the retina and more than 5 mm away from the lens [14].

To reduce intraoperative complications, current randomized controlled trials require inclusion criteria of patients with vitreous floaters lasting more than 6 months and completed posterior vitreous detachment [7, 15], which is not clinically practical. Many patients require intervention in the early stages of symptoms. There is a lack of research on the safety and efficacy of early YAG laser vitreolysis. Therefore, we undertook this clinical study to uncover that early YAG laser vitreolysis is both a safe and effective treatment option for vitreous floaters.

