### Primary outcome

The study will measure the outcomes at 3, 6, 9, and 12 months. These outcomes include the subjective improvement in floater symptoms, which is rated on a scale of 0 to 10. A score of 0 represents no symptoms, while a score of 10 indicates symptoms that significantly impact daily life. The study also measures the mean change in the National Eye Institute Visual Functioning Questionnaire-25 (NEI VFQ-25), which is a self-reported questionnaire that evaluates a patient’s visual function and its effect on their quality of life. The VFQ-25 consists of 25 items, which assess different domains of vision-related quality of life, including general vision, near and distance activities, driving, social functioning, and mental health. The minimum score for the VFQ-25 is 0, indicating the worst possible visual function and quality of life, while the maximum score is 100, representing the best possible visual function and quality of life. Higher scores on the VFQ-25 indicate better outcomes, indicating that the patient has improved visual function and quality of life. To address multiple comparisons in our study, we applied a Bonferroni correction. This correction method adapts the significance level to maintain an overall alpha level of 0.05, effectively controlling for the heightened risk of type I error associated with multiple testing.

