### Statistics analysis

A comprehensive analysis is performed to delineate the demographic and clinical characteristics of the patient population. The normality of the variables is assessed using the Shapiro–Wilk test. The evaluated variables are depicted in tabular form, displaying both absolute and relative frequency distributions. Associations are examined utilizing either Pearson’s chi-square test or Fisher’s exact test, as warranted. The statistical significance of mean differences among quantitative variables is assessed through the paired and unpaired *t*-student tests. To assess variations across different time points within a group, the analysis of variance (ANOVA) with repeated measures is employed.

Continuous data are presented as mean ± standard deviation (SD), while categorical data are represented as counts (percentages). All analyses follow a two-tailed approach, with a significance level of 0.05. The statistical software package SPSS 17 (IBM Corporation, Armonk, NY) is employed for conducting data analysis, by established procedures.

In instances of data discontinuity, missing data will be handled by the “intention-to-treat” principle for conducting inferential statistical analysis. Missing data will be addressed through a dual strategy involving the last observation carried forward (LOCF) method and multiple imputation (MI). Additionally, sensitivity analyses will be conducted to evaluate the influence of various imputation methods on the study outcomes.

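### The stated 90% power is for one test at an unadjusted 0.05, but the primary outcomes are Bonferroni-corrected with no divisor given; power is about 83% with two tests and about 66% with eight

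*Protocol article*

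**What the plan says.** The Sample size calculation section of the protocol article rests on one contrast, "assuming a modest improvement of 30% in symptoms in the YAG group compared to 10% in the sham group". It reports "a sample of 66 patients with a standard deviation of 25%, an alpha level of 0.05, and a statistical power of 0.9", raised to 70 for 5% loss to follow-up.

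The Primary outcome section describes two outcomes, the 0–10 symptom rating and the change in NEI VFQ-25, and states: "The study will measure the outcomes at 3, 6, 9, and 12 months". The same section adds: "To address multiple comparisons in our study, we applied a Bonferroni correction". It explains that this holds the overall alpha at 0.05, but not how many comparisons the correction covers.

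The Statistics analysis section names the unpaired t-test among its methods for differences in means and says: "All analyses follow a two-tailed approach, with a significance level of 0.05".

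Under the Methods paragraph of the Abstract, the early arm has YAG laser at once and sham at 3 months. The delayed arm has sham first and YAG laser at 3 months.

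**The concern.** A sample size should be worked out at the significance level at which the primary test will be judged. Here the calculation gives the whole 0.05 to one test, while the Primary outcome section divides 0.05 among at least two. The adjusted level is then 0.025 or smaller, and 66 evaluable patients no longer give the stated power.

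A real effect of the planned size would be missed more often than the 10% of the time that the protocol implies. A non-significant result might then be read as evidence that early laser does not help, by readers who believe the trial had 90% power. Because the divisor is not written down, they also cannot tell how large the shortfall is.

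**Working it through.** **Inputs.** The Sample size calculation section gives a difference of 30 − 10 = 20 percentage points, SD 25, alpha 0.05 and power 0.9. Randomization and masking gives 1:1 allocation. Statistics analysis gives two-sided testing and the unpaired t-test.

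**Step 1: reproduce the plan's figure.** The normal-approximation formula per arm is

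n = 2 × (z₁₋α/₂ + z₁₋β)² × (SD/difference)²

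n = 2 × (1.960 + 1.282)² × (25/20)² = 32.8, so 33 per arm and 66 in total.

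Allowing for loss, 66/0.95 = 69.5, so 70. Both figures match the article. The t-test version needs 34 per arm (68). A one-sided test would give 54, and reading 30% and 10% as proportions would give 164; neither matches. So the 66 is a single two-sided comparison of means at 0.05, with no multiplicity allowance.

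**Step 2: power at the adjusted alpha.** With 33 per arm the noncentrality is

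20 / (25 × √(2/33)) = 3.25.

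Normal-approximation power is Φ(3.25 − z₁₋α/₂), where α is the per-test level. The t-test power uses the noncentral t distribution with 33 + 33 − 2 = 64 degrees of freedom.

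| Tests in the family | Per-test alpha | Power, t-test | Power, normal | Evaluable total for 90% (normal – t-test) |
|---|---|---|---|---|
| 1 (as planned) | 0.05 | 89.3% | 90.1% | 66 – 68 |
| 2 (two outcomes) | 0.05/2 = 0.025 | 82.7% | 84.3% | 78 – 82 |
| 4 (time points within an outcome) | 0.05/4 = 0.0125 | 74.9% | 77.4% | 90 – 94 |
| 8 (two outcomes × four time points) | 0.05/8 = 0.00625 | 66.3% | 69.7% | 102 – 106 |

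**Step 3: the most favourable retention.** If all 70 were evaluable (35 per arm), power would be 85% by t-test or 87% by normal approximation with two tests, and 70% or 73% with eight. Every value stays below 90%.

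**Step 4: which test the figures describe.** The sized contrast is YAG against sham. It exists only until the delayed arm receives its own laser at 3 months. On the assumption that the month-3 assessment comes before that laser, the figures apply to the symptom score at month 3. At later visits both arms have been treated and a 20-point difference is not what was planned. The 66% is therefore the power of the month-3 symptom test when alpha is divided by eight. It is not the power of each of eight tests.

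**The case against.** The strongest reply is that the article never defines the Bonferroni family. The correction might cover the two outcomes, all eight tests, or only follow-up comparisons after the repeated-measures ANOVA, and a condensed article may leave the divisor to the analysis plan. This stands in part: 83% to 66% is a range over readings, and no single value in it is the plan's own. But the correction is stated under Primary outcome as the means of keeping the overall alpha at 0.05. With two primary outcomes, the divisor that does this is at least 2, and that alone rules out 90%.

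It also stands that the two-outcome reading leaves power above the customary 80%, and that part of the fall to 83% is a change of formula (89.3% by t-test against 90.1% by normal approximation, before any correction). These are per-test powers as well. The chance of success on at least one primary outcome is higher, but the article gives no effect size or SD for NEI VFQ-25 from which to work it out. Sizing a trial on one outcome is common and is not itself a fault here.

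Two stronger readings are tempting, and the document does not support them.

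- A reader might infer that the plan contains two rival rejection rules, Bonferroni in one section and an unadjusted 0.05 in another. The Statistics analysis sentence can be read as giving the overall level, which agrees with the Primary outcome section. It needs clarifying, but it is not a proven contradiction.
- A reader might infer that power is lower still because the sham assumption cites earlier trials, and the Background says that "current randomized controlled trials require inclusion criteria of patients with vitreous floaters lasting more than 6 months", whereas this trial enrols at about one month. Spontaneous adaptation could occur in both randomized arms. If both improve equally, the 20-point difference and the power are unchanged. The article gives no size or timing for adaptation, so a lower power figure on this ground would be speculation.

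**Conclusion.** The stated 90% power does not hold under the protocol's own multiplicity rule. For the planned symptom effect, power is about 83% by t-test (84% by normal approximation) if Bonferroni covers the two outcomes, and about 66% (70%) if it covers all eight outcome-by-time tests. The chance of missing that effect is thus about 17% to 34% by t-test, against the 10% implied.

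This rests on the planned difference of 20 and SD of 25, on 33 evaluable patients per arm, on a divisor between 2 and 8, and on a month-3 assessment made before the delayed arm's laser. The Abstract lists visits at 1, 3, 6 and 12 months rather than 3, 6, 9 and 12; either list has four time points, so the range does not change. That power falls short of 90% is certain for any divisor of 2 or more. How far it falls depends on a number the article does not give.

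**What to change.** Three changes of wording suffice:

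1. In Primary outcome, state which comparisons the Bonferroni correction covers and the divisor.
2. In Sample size calculation, restate the power at the resulting alpha: about 83% for two tests or about 66% for eight, by t-test with 33 per arm.
3. In Statistics analysis, say that 0.05 is the overall level and refer to the adjusted level for the primary tests.

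The cost is a less favourable stated power; no visit, procedure or enrolment target changes.

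If the sponsor wants to keep about 90%, an option is to make the month-3 symptom score the single primary test at two-sided 0.05, test NEI VFQ-25 at month 3 next in fixed sequence at 0.05, and make later time points secondary. This is more than wording. It changes the primary endpoint of a trial that had enrolled 32 participants by 19 September 2023. It therefore needs an amendment before unblinding, with the ethics approval and registry entry that the Data collection, management, and monitoring section requires. NEI VFQ-25 could then be claimed only if the symptom score succeeds, and the comparison of early with delayed treatment after month 3 would become secondary.

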**Methods:**

The present study is a randomized, controlled, double-blind clinical trial. A total of 70 participants with symptomatic floaters for 1 month were prospectively recruited. These participants will be randomly assigned to two groups, with 35 individuals in each group: the early treatment group and the delayed treatment group. Participants assigned to the early treatment group will undergo YAG laser vitreolysis immediately, followed by a sham laser treatment 3 months later. On the other hand, participants assigned to the delayed treatment group will receive a sham laser treatment and then undergo YAG laser vitreolysis 3 months later. The follow-up time points will be 1, 3, 6, and 12 months from randomization. Primary outcomes will be participants’ self-reported improvement in visual disturbance on a scale of 1 to 10 and their scores on the National Eye Institute Visual Functioning Questionnaire 25 (NEI VFQ-25). Secondary outcomes will be an objective evaluation of the effectiveness of the treatment in reducing vitreous floaters through OCT and fundus photography and tracking any adverse events related to the eyes or overall health.

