### Randomization and masking

In this study, a stratified randomization method will be used to allocate participants to two groups in a 1:1 ratio, using SPSS v26.0 (SPSS Inc, Chicago, IL, USA). The randomization process incorporates minimization and involves the consideration of three study variables for group stratification: sex (male/female), age (> 50/ ≤ 50 years), and crystal state (phakic eye/pseudophakic eye). A random allocation sequence will be created in advance and sealed in sequentially numbered opaque envelopes, allowing for randomization one at a time. Group allocation will be carried out by another researcher to ensure the randomization process is unbiased. All researchers involved in the study, including outcome assessors, statisticians, and data analysts, will be blinded to group assignment, but those providing the intervention will be informed as necessary. Before the trial, researchers will undergo comprehensive training in the randomization procedure and will be made aware of their responsibilities. The successful implementation and maintenance of the randomization and blinding methods will be validated to ensure the reliability and absence of bias in the trial results.

The investigator is strongly advised to uphold the blinding to the greatest extent possible. The actual allocation should not be revealed to the patient or any other study personnel, including site personnel, monitors, or project office staff. There should also be no written or verbal disclosure of the code in any of the patient-related documents associated with the study.

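### The stated 0.9 power is for the symptom rating at an uncorrected alpha of 0.05; under the protocol's own Bonferroni correction it is about 83-84% for a family of two tests, and lower for a larger one

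*Protocol article*

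**What the plan says.** The Sample size calculation section rests on a single contrast, "assuming a modest improvement of 30% in symptoms in the YAG group compared to 10% in the sham group". It continues "This results in a sample of 66 patients with a standard deviation of 25" (the SD is in per cent), with "an alpha level of 0.05, and a statistical power of 0.9". Loss to follow-up is then added: "To account for a 5% rate of lost follow-up, it was decided to include 70 subjects in the study". The section mentions neither the NEI VFQ-25 nor any multiplicity correction.

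The abstract names two primary outcomes, self-reported "improvement in visual disturbance on a scale of 1 to 10 and their scores on the National Eye Institute Visual Functioning Questionnaire 25". The Primary outcome section repeats both, lists assessments at 3, 6, 9 and 12 months without singling out one of them, and applies a Bonferroni correction. Of that correction it says: "This correction method adapts the significance level to maintain an overall alpha level of 0.05". It does not say how many tests the correction covers.

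The Statistics analysis section fixes the sidedness: "All analyses follow a two-tailed approach, with a significance level of 0.05". It names unpaired t-tests for differences in means.

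**The concern.** If 0.05 is the overall level across several primary tests, no single one of them is run at 0.05. A power figure worked out at 0.05 then describes a test that the protocol does not plan to use. The Bonferroni sentence stands in the Primary outcome section, after the two outcomes and the four visits, so its natural subject is the primary comparisons.

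What is at stake is how a null result would be read. A reader who credits the trial with 90% power would take a non-significant symptom rating as fairly strong evidence against an effect of the assumed size. In fact the chance of missing that effect is clearly above 10%. The type I error is not in question.

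**Working it through.** **Inputs.** Mean improvement 30% v 10%, so a difference of 20 points; SD 25; 66 evaluable; 70 enrolled after a 5% allowance (all from Sample size calculation). Allocation 1:1, so 33 or 35 per arm (Randomization and masking: "allocate participants to two groups in a 1:1 ratio"). Two-sided unpaired t-test (Statistics analysis). Two primary outcomes, four visits, overall alpha 0.05 (Primary outcome).

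**Step 1: reproduce 66 and 70.** The normal formula is n per arm = 2 × (z for 1 − α/2 + z for power)² × (SD/difference)².

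- At two-sided 0.05 and power 0.9: 2 × (1.960 + 1.282)² × (25/20)² = 2 × 10.51 × 1.5625 = 32.8, so 33 per arm and 66 in total.
- Allowance for loss: 66/0.95 = 69.5, so 70.

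Both figures match. Other readings do not fit. A comparison of two proportions, 30% v 10%, needs 82 per arm, and one-sided 0.05 needs 27 per arm. One-sided 0.05 split over two tests would also give 66, but the protocol makes all analyses two-tailed. The correction was therefore not built into the sample size.

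**Step 2: corrected alpha.** For two outcomes at one time point, 0.05/2 = 0.025 per test. For two outcomes at four visits, 0.05/8 = 0.00625. The abstract's follow-up list (1, 3, 6 and 12 months) differs from the Primary outcome section's list, but it also has four visits and so also gives eight.

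**Step 3: power of one test of the symptom rating.** Standardised difference 20/25 = 0.8. The normal approximation is Φ(0.8 × √(n/2) − z for 1 − α/2). With n = 33, 0.8 × √16.5 = 3.250:

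- α = 0.05: Φ(3.250 − 1.960) = Φ(1.290) = 0.901
- α = 0.025: Φ(3.250 − 2.241) = Φ(1.008) = 0.843
- α = 0.00625: Φ(3.250 − 2.734) = Φ(0.515) = 0.697

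The noncentral t uses the same noncentrality with 2n − 2 degrees of freedom. Results by both methods:

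| Two-sided α per test | 33 per arm, t | 33 per arm, normal | 35 per arm, t | 35 per arm, normal |
|---|---|---|---|---|
| 0.05 (no correction) | 0.8926 | 0.9014 | 0.9097 | 0.9172 |
| 0.025 (two tests) | 0.8274 | 0.8433 | 0.8515 | 0.8655 |
| 0.00625 (eight tests) | 0.6628 | 0.6968 | 0.6985 | 0.7298 |

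Within one method, going from one test to two at 33 per arm costs 6 to 7 points: 90.1% to 84.3% (normal) or 89.3% to 82.7% (t).

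**Step 4: type II error against the stated 10%.** By the t calculation at 33 per arm, it is 100 − 82.7 = 17.3% for two tests, 1.7 times the stated value. For eight it is 100 − 66.3 = 33.7%, 3.4 times. By the normal formula the figures are 15.7% and 30.3%.

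**Step 5: for scale only.** Holding 90% for the symptom rating would need 39 per arm (normal) or 41 (t) at 0.025, and 51 or 53 at 0.00625, before loss to follow-up.

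**The case against.** **The family is not defined, and an analysis plan may define it.** This stands for the size of the shortfall but not for its existence. The largest power for the symptom rating in any Bonferroni family of two or more tests is the 86.6% in the table (two tests, all 70 analysed, normal formula). The correction could be meant only for the repeated-measures ANOVA within groups, but its place in the Primary outcome section and its reference to an overall alpha speak against that.

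**83% might be read as a ceiling.** It is not one. It is the t figure for 66 evaluable. The protocol plans intention-to-treat analysis with imputation, and with all 70 contributing full information the figure is about 85-87%. Imputation does not fully restore what is lost, so the truth may lie between.

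**66% might be read as the power of the whole set of listed tests.** The document does not support that. It is the power of one test if eight share the alpha. No text says that eight between-group tests form the family. The assumed 30% v 10% contrast is laser against sham, and it exists only up to month 3; the delayed group then receives the real laser. Carrying a standardised difference of 0.8 to months 6, 9 and 12 is not the protocol's assumption.

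**The trial might be said to lack power overall, or to have ample power.** Either depends on a success rule the article does not give. If the NEI VFQ-25 also had a standardised difference of 0.8 (assumed; the protocol gives no effect or SD for it), 33 per arm at 0.025 each would give about 68% to 75% power for both outcomes to succeed, for correlations from 0 to 0.7. For at least one to succeed it would be about 97% at correlation 0 and 91% at 0.7, falling to 88% at 0.9. Neither figure can be attributed to the protocol, whose power claim concerns symptoms only.

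**Conclusion.** The point holds as a mismatch between two sections of the protocol. The 0.9 is right for the symptom rating at an uncorrected two-sided 0.05 and does not hold for the corrected test that the Primary outcome section prescribes. Per-test power for that outcome is about 83-84% with 66 evaluable, or 85-87% with all 70, if the family is the two outcomes at one time point. It falls to about 66-70% with 66 evaluable if the family is all eight comparisons. The family size is an inference in both cases. The figures assume the protocol's difference of 20 and SD of 25, which apply to the laser-versus-sham period up to month 3. The range within each pair reflects the t and normal calculations.

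A reader might infer that 70 patients are too few or that the primary analysis is invalid. Neither follows: the correction protects the type I error, and under the two-test reading power remains above 80%. This is a statement that should be corrected, not a reason to change the size of the trial.

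**What to change.** Keep 70 patients and make two edits.

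1. In the Primary outcome section, state which comparisons form the Bonferroni family, by outcome and visit, and the resulting alpha per test.
2. In the Sample size calculation section, restate the power at that alpha. If the sponsor chooses the two outcomes at one time point, suitable wording would be: with 33 evaluable per arm, power is about 83% for the symptom rating at two-sided 0.025; no power is claimed for the NEI VFQ-25. If the sponsor keeps all eight comparisons, the figure is about 66% for a single test, with a note that the assumed contrast applies only up to month 3.

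The choice of family and time point is the sponsor's, since the document fixes neither. It should be made before any unblinded look at outcome data.

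Optionally, to keep about 0.9 for the symptom rating without more patients, replace Bonferroni with a fixed order: the symptom rating at one named visit at 0.05, then the NEI VFQ-25 at 0.05 only if the first test is significant. This changes the testing procedure and not just the power statement.

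The cost is a less favourable stated power and a short amendment. The protocol requires ethics committee approval and a registry entry for modifications. Recruitment was still open at the reported date, with 32 enrolled by 19 September 2023 and closing extended to December 2024.
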